## Discussion

### Potential impact and significance of the study

This massage protocol was created from recent findings in the literature and its standardization was performed according to the union of the best results found. The implementation and use of this standardized protocol will provide important and reliable information regarding the use of massage in post-exercise recovery, with the identification of its effects on the ANS and the best moment and form of massage application, representing an important advance in the sports field and in clinical practice.

### Strengths and limitations of this study

A strong point of this study is that the protocol created was based on the latest in the literature on the theme. Another strong point of the study is the comparison of the effects of massage when applied at different moments on post-exercise recovery. In addition, its design of a randomized clinical trial of the cross-over type, the easy reproducibility of the protocol from the description of the same, the fact of the massage being performed by three physiotherapists specialized in sports physiotherapy also enhances the study. However, one limitation of this study is the impossibility of blinding the physiotherapists and participants regarding the application of the technique, and although standardized there is no control of the pressure exerted during the massage, only a subjective control through the level of comfort of the volunteer with the specific scale application.

### Contribution and clinical applicability

With the accomplishment of this study we will verify which HRV indices demonstrate a significant influence of the massage in post-exercise recovery, and which moment of application presents better recovery after exercise. The data obtained in the present study will provide subsidies for the best management of application of the technique in sports clinical practice, considering periods of training and, mainly, of competitions.

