**Methods:**

This is a randomized, cross-over clinical trial. Forty men aged 18 to 30 years, healthy and physically active according to the International Physical Activity Questionnaire will participate in the study. Participants will be randomized into groups, which will perform the five interventions of the study at randomized moments, one intervention per session: Intervention 1: control; Intervention 2: participants will receive the massage protocol; Intervention 3: performance of the stress protocol; Intervention 4: participants will perform the stress protocol and immediately after receive the massage; Intervention 5: participants will perform the stress protocol and 1 h after conclusion of the protocol will receive the massage. The sessions will occur with an interval of 1 week between them and, due to the technique used, blinding participants and therapists is not possible. The primary outcome measure is HRV that will be measured 2 h after the conclusion of each intervention, and secondary outcome measures, which include heart rate, respiratory rate, blood pressure, oxygen saturation, and individual touch perception, will be measured at specific moments in the course of each intervention.

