### Outcomes

The primary outcome will be the evaluation of autonomic modulation of heart rate by means of HRV. Secondary outcomes are cardiorespiratory parameters (blood pressure, heart rate, respiratory rate, and oxygen saturation) and individual touch perception. Evaluations will be performed by the same independent trained assessors throughout the study.

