#### Primary outcome

HRV will be used as the primary outcome as it is an important overall marker of post-exercise recovery [16]. The HRV analysis will be performed from the series of RR intervals captured by the cardiofrequency meter Polar Electro Oy – model V800, and linear methods analyzed in the time domain and frequency domain, and Poincaré plot. All HRV indices will be obtained through the *software* Kubios HRV – version 2.0 [20].

For this analysis, the time series of RR intervals will initially be subjected to digital filtering using the *software* Kubios HRV – version 2.0, supplemented by manual filtering, to eliminate premature ectopic beats and artifacts, and only series with more than 95% of sinus beats will be included in the study [20]. Through visual analysis of the time series, the absence of ectopic artifacts or beats that can interfere in the HRV analysis will be observed.

During the recovery period, the evaluated moments will be: R1 (initial 5 min of rest before performing the interventions), R2 (initial 5 min of recovery), R3 (fifth to 10th minutes of recovery), R4 (10th to 15th minutes of recovery), R5 (20th to 25th minutes of recovery), R6 (30th to 35th minutes of recovery), R7 (40th to 45th minutes of recovery), R8 (50th to 55th minutes of recovery), R9 (60th to 65th minutes of recovery), R10 (70th to 75th minutes of recovery), R11 (90th to 95th minutes of recovery), and R12 (115th to 120th minutes of recovery). It is worth mentioning that 256 consecutive RR intervals will be obtained at these moments [21].

HRV indices in the time domain (rMSSD and SDNN), frequency domain (low-frequency spectral component (LF) and high-frequency spectral component (HF)), and the Poincaré plot (SD1 and SD2) will be evaluated [22].

In the time domain, the rMSSD Index corresponds to the square root of the square mean of the differences between the adjacent normal RR intervals in a time interval expressed in milliseconds and evaluates the behavior of the parasympathetic autonomic modulation [22], while the SDNN Index represents the standard deviation of all normal RR intervals recorded in a time interval, expressed in milliseconds, and is considered a measure of global variability, that is, it evaluates both sympathetic and parasympathetic modulation [22].

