### Sample size

As described above the primary outcome will be the HRV. The sample size calculation was carried out based on the study of Arroyo-Morales et al. [15] in which the SDNN Index of the HRV was selected, since it is an index that expresses the behavior of the ANS in a global way. To establish the sample size, a mean effect of 26.9 and standard deviation of 38.8 were chosen. The level of significance for the sample size is 5%, the power test is 80%, two-tailed test, and 10% of the total value of *n* is added to statistically supply the analyses in the case of withdrawals during data collection. The value obtained for the sample size was 33 participants, adding the 10% gave a sample of 36 volunteers. However, there are other indices besides the SDNN Index within the HRV, and this situation generates an environment where the sample size could be underestimated. In the same sense, due to the new proposal presented by the study, there are no trials in the literature that have the same proposal dynamics, and thus, for safety we will add four volunteers to ensure the statistical analysis of all HRV indices, thus totaling a sample of 40 participants.

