### Statistical analysis

For analysis of the data of the population profile, the descriptive statistical method will be used and the results presented as values of means, standard deviations, median, minimum and maximum numbers, and confidence interval. The normality of the data will be evaluated through the Shapiro-Wilk test.

The comparisons of cardiorespiratory parameters and HRV indices between interventions (I1, I2, I3, I4, and I5) and moments (rest (R1) vs recovery moments (R2–R12)), the data are analyzed from the prism of the covariance analysis (ANCOVA), which will be adjusted for the baseline value of the evaluated variable and generated estimated means after such adjustment (extracting the variance explained by the confounding variables). The Levene test will be used to prove the homogeneity of the variances at the created moments, and the Bonferroni post hoc test will be used for comparison. To guarantee homogeneity of data the variable can will be transformed into logarithm.

For analysis of the moments (rest vs recovery moments), repeated measures ANOVA with the Tukey post test for parametric distribution or Friedman test with Dunnett’s post test for non-parametric distribution will be used and the analysis of the different groups will be performed by means of one-way ANOVA with the Tukey post test or the Kruskal-Wallis test with Dunnett’s post test.

The level of significance will be *p* < 0.05 for all tests. The SPSS statistical program (version 13.0) (SPSS Inc., Chicago, IL, USA) will be used for the analyses. Data integrity will be monitored by regularly scrutinizing data files for omissions and errors. Participants will be given an anonymous study ID to protect confidentiality, and only study investigators will have access to the final trial data set.

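### No primary HRV index or recovery moment is fixed: type I error is uncontrolled across six indices and, as far as stated, across eleven moments

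*Protocol article*

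**What the plan says.** All references are to the protocol article.

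- **Outcomes:** "The primary outcome will be the evaluation of autonomic modulation of heart rate by means of HRV". No single index is named.
- **Primary outcome:** the indices are introduced as "HRV indices in the time domain (rMSSD and SDNN), frequency domain" (LF and HF), followed by SD1 and SD2 from the Poincaré plot. That makes six. Each is taken at rest (R1) and in eleven recovery windows, R2 to R12.
- **Abstract, Methods:** "The primary outcome measure is HRV that will be measured 2 h after the conclusion of each intervention". This can be read as one time point or as a two-hour follow-up.
- **Sample size:** for the calculation, "the SDNN Index of the HRV was selected, since it is an index that expresses the behavior of the ANS in a global way". The section concedes that there are other indices and adds four volunteers on that account.
- **Statistical analysis:** "The level of significance will be *p* < 0.05 for all tests". For the ANCOVA across interventions and moments, "the Bonferroni post hoc test will be used for comparison". For the separate group analysis the plan is "one-way ANOVA with the Tukey post test or the Kruskal-Wallis test with Dunnett’s post test".
- **Study interventions:** I1 to I3 provide reference behaviour. The question about massage and its timing is put to I4 and I5.
- **Contribution and clinical applicability:** "we will verify which HRV indices demonstrate a significant influence of the massage in post-exercise recovery".

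**The concern.** A sample size calculation at 5% and 80% describes one test. This trial will run many and names none of them as the one on which the conclusion rests. The post tests deal with multiple intervention pairs. They do not deal with having six indices on which a pair can differ, or, unless the Bonferroni step is meant to reach that far, eleven windows in which it can differ.

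The four added volunteers are offered as the answer to the extra indices. A larger sample raises power, but the false-positive rate of a test run at a given level does not depend on the sample size. At stake is the promised advice on whether and when to apply massage after exercise: one significant index in one window could carry it.

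**Working it through.** **1. The plan's own figure.** Inputs from the sample size section: effect 26.9, SD 38.8, two-sided 5%, power 80%.

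n = 2 × (1.960 + 0.842)² × 38.8² / 26.9² = 32.7, so 33. Then 33 × 1.10 = 36.3, so 36, and 36 + 4 = 40.

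The figures reproduce. They correspond to a single comparison of a single index at 0.05, with no allowance for several indices, moments or pairs.

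**2. Count of tests.** Six indices × 11 moments = 66 index-by-moment combinations. Five interventions give 5 × 4 / 2 = 10 pairs.

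Two of the six indices are essentially one. With ΔRR the difference between adjacent intervals, SD1² = ½ Var(ΔRR) and rMSSD² = Var(ΔRR) + mean(ΔRR)². So SD1 equals rMSSD/√2 apart from drift. A numerical check gave rMSSD 43.387 against SD1 × √2 = 43.386. That leaves five distinct indices and 5 × 11 = 55 tests per pair.

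**3. Level per test under the stated plan.** Bonferroni over ten pairs gives 0.05 / 10 = 0.005 for each pair within each index and moment.

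**4. Contrasts that carry the aim.** These are I4–I3, I5–I3 and I4–I5: 3 × 55 = 165 tests at 0.005. If all were independent, the chance of at least one false positive would be 1 − 0.995^165 = 0.56. They are not independent, so the null case was simulated: n = 36, paired t-tests, five indices with a common correlation, eleven moments with first-order serial correlation. The protocol gives none of these correlations, so they were varied.

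| Between-index and adjacent-moment correlation | Bonferroni over 10 pairs | Bonferroni over 10 pairs × 11 moments |
|---|---|---|
| 0.5 to 0.8 | about 26% to 47% | about 4% to 6% |
| 0.9 | about 15% | lower still |

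A fresh run of 4,000 replicates per setting gave 28% to 46% and 16% in the first column, and 4% to 7% and 2.5% in the second. This agrees within simulation error and small differences in set-up.

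**5. Reference case.** One SDNN value per session, with the three contrasts tested at 0.05 / 3 = 0.0167 each, keeps the chance of any false claim at or below 5% by construction (4.0% to 4.7% in the same run).

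**The case against.** **The pairs are adjusted.** A reader might infer that some 6 × 11 × 10 = 660 tests are each run at 0.05, and that a false claim for massage or its timing is therefore more likely than not. The documents do not support that. The statistical analysis section plans Bonferroni, Tukey or Dunnett's post tests. Rates above 50% at correlations of 0.5 to 0.8 arise for a single pair tested without adjustment (58% to 86%), which is not the plan. They also arise when any of the ten pairs is counted (57% to 82%). Those ten include pairs such as I1 against I3, which contain no massage. For the three contrasts that carry the aim, the rate stays below 50%. Counting I2–I1 as well would raise it somewhat.

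**Bonferroni may reach the moments.** The ANCOVA sentence covers interventions and moments together, so the correction may span both. The three-contrast rate would then be near 5%. This stands as a possibility; the text does not settle it.

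**Pairing may be ignored.** If the one-way ANOVA were used on these crossover data, the Bonferroni-adjusted rate for the three contrasts would be about 1% to 2% at an assumed within-person correlation of 0.5. That comes from an over-wide standard error, not from error control, and it still identifies no primary test.

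**The closing sentence is not an analysis rule.** It stands in the discussion and shows intent. The moment of application mentioned there is the timing of massage, I4 against I5, and not a recovery window. It should not be read as a plan to report whichever window is significant.

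**The abstract may only be loosely worded.** The intervention descriptions speak of two-hour follow-up, and the abstract probably means the same. It needs aligning, but it is not firm evidence of a rival single time point.

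None of this supplies a primary index or a rule across indices.

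**Conclusion.** The point holds in this form. No HRV index or recovery moment is designated primary, no adjustment is stated across the six indices, and it is unclear whether the eleven moments are covered. The four extra volunteers do not bear on type I error.

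The inflation for I4–I3, I5–I3 and I4–I5 is about 26% to 47% against a nominal 5%, and about 15% at correlations of 0.9. This assumes within-person tests, Bonferroni over the ten pairs only, and the assumed correlation structure. It falls to near 5% if the Bonferroni step also covers the moments. The exact rate cannot be had from the document; the absence of an identified primary test can. The documents do not support saying that a false massage claim is more likely than not.

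**What to change.** - Name SDNN, the index used for sizing, as the sole primary index.
- Fix in advance one R1-adjusted SDNN value per session: either a single recovery window or a summary on a time grid available and comparable for I3, I4 and I5. This needs care. With follow-up counted from the end of a 12-minute massage, I5's windows begin about 60 + 12 = 72 minutes after stress. On that clock I3 then offers only part of R10 (70–75 min), R11 (90–95) and R12 (115–120), and the I5 windows do not fall at the same times.
- Test I4–I3, I5–I3 and I4–I5 as within-person contrasts with Holm at an overall 5%.
- Make the other indices and the window-by-window results secondary or exploratory. Report SD1 and rMSSD as one measure.
- State what the Bonferroni step covers wherever it is kept, and align the abstract's time-point wording.

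No extra participants are needed. Three contrasts instead of ten also cost less power. For the planned effect with n = 36, the SD of the difference is 38.8 × √(2(1 − ρ)). At assumed within-person correlation ρ = 0.3 this is 45.9, and power rises from 70% (level 0.005) to 84% (0.0167). At ρ = 0.5 it is 38.8, and power rises from 87% to 94%. The gain thus depends on a correlation that the protocol does not give.

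The cost is a protocol amendment while recruitment is under way. Significant results on other indices or single windows could also no longer be headline conclusions.

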## Trial status

Number Protocol: NCT03094676

Patient recruitment is currently underway.

Study start date: 9 April 2018

Primary completion date: 14 May 2018

Study Completion date: 30 July 2018

## Abbreviations

ANS: Autonomic nervous system
BMI: Body Mass Index
FCT/UNESP: Universidade Estadual Paulista
HF: High-frequency spectral component
HRV: Heart rate variability
I1: Intervention 1
I2: Intervention 2
I3: Intervention 3
I4: Intervention 4
I5: Intervention 5
IPAQ: International Physical Activity Questionnaire
LF: Low-frequency spectral component
rMSSD: Index corresponds to the square root of the square mean of the differences between the adjacent normal RR intervals in a time interval, expressed in milliseconds
SD1: Instantaneous index of beat-to-beat variability
SD2: Index represents the HRV in long-term records
SDNN: Index represents the standard deviation of all normal RR intervals recorded in a time interval, expressed in milliseconds
